## Abstract

**Background:**

Diabetes education is key to achieving metabolic control and promoting healthy behaviors in people with type 2 diabetes. Mobile health (mHealth) tools have been shown to be an important tool for monitoring, disease care and lifestyle improvement in people with type 2 diabetes (T2D). In less developed countries, the effect of educational intervention through mHealth is still inconclusive. The objective of this study is to evaluate the effect of an intervention on metabolic control in people with T2D with mHealth intervention and educational website called “I understand my diabetes”.

**Methods:**

The study is designed as a 12-month randomized controlled trial with three parallel arms: (1) Web-based education, (2) Web-based education + mobile app (diet and exercise plan), (3) Usual care. The total study duration is 12 months with data collection at baseline, 3, 6, 9 and 12 months. We will enroll 408 Mexican adults with T2D, randomized equally across arms. Measurements at baseline, 3, 6, 9, and 12 months include A1c (primary outcome), lipid profile, anthropometry, body composition, quality of life, lifestyle, and physical activity.

**Discussion:**

The trial will evaluate whether reinforcing diabetes education with an app and educational website improves metabolic outcomes in people with type 2 diabetes. Findings may be relevant for implementation in public institutions with high demand of people with type 2 diabetes who have not presented severe complications of the disease. Integration of mHealth into routine care could enhance self-management and disease control in people with type 2 diabetes.

**Clinical Trial Registration: Trial registration number:**
Clinical Trials.gov**. Registry** (NCT0627857I). The protocol number**:** Effect of Education with Mobile App on metabolic control in Patients With type 2 Diabetes. The registration number R-2018-785-100. Instituto Mexicano del Seguro Social. Mexico. Registration date: February 22, 2024.

## Background

Type 2 diabetes (T2D) is a disease with a significant global impact, according to the International Diabetes Federation (IDF). By 2021, an estimated 536.6 million people (12.2%) were living with T2D, with projections reaching 783.2 million by 2045 (1). This condition is among the leading causes of mortality and disability in Mexico and worldwide (2, 3). The 2022 National Health and Nutrition Survey conducted in Mexico reported a diabetes prevalence of 18.3%, (5.6% newly diagnosed), which is higher than the 16.8% reported in 2018 (4).

The treatment of T2D should be considered by health professionals to promote the adoption of a healthy lifestyle that includes a balanced diet, regular physical activity, and motivation for effective self-care (5, 6).

In this sense, diabetes education should aim to provide patients with the knowledge required for effective self-management of T2D. This includes fostering the adoption of positive health behaviors, encouraging adherence to care recommendations provided by healthcare professionals, and promoting a healthy lifestyle. It has been reported that an adequate lifestyle can prevent up to 37% of macrovascular complications and 24.7% of microvascular complications in people with T2D (7).

The use of technology in the care and treatment of T2D has grown globally, particularly in high-income countries since the inclusion of tools for insulin calculating and tracking, as well as glucose monitoring, and graphing glucose levels (8, 9). In addition, mHealth technologies have been increasingly used to support diabetes education and self-management through mobile devices (10). There is also evidence supporting the effectiveness of mHealth for weight loss among people with T2D (11).

Moreover, m Health has shown potential in helping individuales meet therapeutic goals, including glycemic control through reductions in A1c levels and improvements in other cardiometabolic risk indicators, such as waist circumference (WC). It also contributes to more efficient clinical care of people with diabetes (12).

mHealth has been associated with improvements in self-management, medication adherence, communication with healthcare providers, and the adoption of healthy behaviors (13). However, the scope and effectiveness of its various applications remain under discussion—particularly regarding its use in glucose monitoring, diabetes education, lifestyle interventions (whether autonomous or guided by professionals), and the duration of follow-up strategies (14).

Current mHealth strategies commonly target glucose monitoring, dietary management and insulin dose adjustments, medication adherence, and physical activity. Nevertheless, the number of studies assessing their applicability in routine clinical care for adults with diabetes remains limited (12).

Furthermore, there is a lack of information about comprehensive strategies in developing countries that integrate monitoring, diabetes education, promoting healthy lifestyle habits, and self-care aimed at meeting therapeutic goals in developing countries (15). There is also limited evidence regarding validation of mHealth content by healthcare professionals before implementation. Previous studies have reported the feasibility, acceptability, and usefulness of providing diabetes education for patients through an educational website in both in-clinic and remote formats (16, 17).

In Mexico, 68% of people with T2D have poor glycemic control and limited adherence to non-pharmacological treatment. This is associated with a high prevalence of obesity, dyslipidemia, and arterial hypertension. These risk factors can affect the quality of life and increase costs for public health systems (18).

Our previous research has shown the positive effects of implementing an educational website in a clinical setting, used prior to medical and nutritional consultations. This intervention not only led to sustained improvements in A1c levels over 12 months but also enhanced diabetes-related knowledge and healthy lifestyle adoption among people with T2D (19–21).

The objective of the present study is to evaluate the effect of a digital intervention “I Understand My Diabetes” on metabolic control in people with T2D. The intervention includes a mHealth component and an educational website, designed and adapted to the needs of patients attending the health institute that serves the largest population of people with diabetes in Mexico. The intervention follows international clinical trial guidelines and recommendations (https://www.ctti-clinicaltrials.org).

## Methods/design

### Objectives

The primary objective of this clinical trial is to assess changes in A1c when comparing web-only, web + app, and usual care.

The secondary objectives are to evaluate the effect of the intervention on:
Lipid profile [total cholesterol, LDL-c [low-density lipoprotein cholesterol], HDL-c [high-density lipoprotein cholesterol], and triglycerides].Body composition and anthropometric measurements (body fat percentage, body fat mass, weight, BMI [body mass index], and waist circumference).Quality of life (Diabetes 39, validated in the Mexican population).Lifestyle (IMEVID, validated for diabetes population in Mexico).Level of physical activity [IPAQ (International Physical Activity Questionnaire)].

### Design and setting

A randomized controlled trial with three parallel groups, will be conducted across seven family medicine clinics of the Mexican Social Security Institute in Mexico City. The duration of intervention and follow-up is 12 months, with evaluations at baseline, 3, 6, 9 and 12 months. This study complies with international ethical standards and was approved by the National Research and Ethics Commission of the Mexican Social Security Institute, under the registration number R-2018-785-100. The clinical trial considers the effect of the mobile app + website vs. the website alone and a control group. It assumes a minimum clinically important difference (MCID) of 0.5% in HbA1c at 12 months. Based on the findings reported by Duke et al. (Cochrane 2009; ref. 23), who reported modest mean reductions in HbA1c with individual education (−0.3% in participants with a baseline HbA1c > 8%), a reduction of 0.5% was considered; a standard deviation (SD) of 1.3% was assumed based on reports from primary care cohorts and registry data, where the SD of HbA1c typically ranges from 1.1% to 1.3%. Using the formula to compare two means with *α* = 0.05 (two-tailed) and 80% power: *n* per group = 2 × (Z1 − *α*/2 + Z1 − *β*)2 × *σ*2/*Δ*2 With Z1 − 0.025 = 1.96, Z0.80 = 0.84, *σ* = 1.3, and *Δ* = 0.5, the required sample size was 106 participants per group. Taking into account a 20% loss, this resulted in 133 per group, and for greater conservatism, 136 participants per group were recruited (22).

### Selection criteria

The study will involve adults who have been previously diagnosed with T2D by their treating physician, with A1c > 7% and < 13%, with and without pharmacological treatment for diabetes (hypoglycemic agents or insulin). Participants >65 years old with ≤10 years of diabetes diagnosis

Participants with severe complications of the disease (chronic renal failure, blindness, or amputation), requiring specialized medical and nutritional care will be excluded as well as people with morbid obesity (BMI ≥ 35 kg/m^2^). Selection criteria for the study are described in Figure 1.

**Figure 1 F1:**
[figure not shown]
Selection criteria.

### Protocol management

The objectives and activities of the project will be explained to the authorities and permission will be requested to conduct the study at the selected clinics. The participating researchers will provide information about the study to the patients, answer their questions and, once people decide to participate voluntarily, ask for informed consent.

### Biochemical measurements

After a 12 h fasting period, venous blood samples will be obtained from participants. A1c levels will be measured using high-performance liquid chromatography. Serum levels of fasting glucose, total cholesterol, LDL-c, HDL-c, and triglycerides will be analyzed using automated photometry. They will be measured using the automated photometry method [Roche Cobas 800 c701). Samples, properly stored at all centers, will be sent in special containers to be processed at a certified central laboratory.

### Anthropometry and body composition measurements

Anthropometry will be recorded by two previously trained nutritionists and standardized according to the method proposed by Habitch and the specifications described by Lohman et al. (23, 24) Weight (kg) and height (cm) will be obtained for the calculation of BMI in an Inbody® device (model BPMO40S12F07). Additionally, WC will be measured at the midpoint between the lower rib and the upper edge of the superior iliac crest on the right side. Hip circumference (HC) will be measured at the greater diameter of the trochanters. The measurements will be recorded three times and the mean value of the second and third measurements will be used for analysis.

Body composition will be assessed using bioelectrical impedance analysis (BIA). At the UMF 20 clinic, measurements will be obtained with the InBody 120 device (InBody Co.), while at the remaining sites (UMF 1, 4, 7, 9, and 10), an Omron body composition monitor (Omron Healthcare) will be used.

All measurements will be performed under standardized conditions. Participants will be instructed to fast for at least 8 h, refrain from alcohol, caffeine, and strenuous exercise for 24 h prior to the assessment, and empty their bladder immediately before the test. Measurements will be taken with participants in light clothing, barefoot, and standing upright, following the manufacturer's operating guidelines for each device. The InBody 120 applies a multifrequency electrical current through hand and foot electrodes, while the Omron devices use a single-frequency current with footplate electrodes. Both methods estimate body composition using proprietary algorithms. The following variables will be recorded: body weight (kg), body mass index (BMI), body fat percentage (%), fat mass (kg), skeletal muscle mass (kg), and total body water (liters) will also be documented. To ensure consistency and reproducibility, all measurements will be conducted by trained personnel, using the same device for each participant at baseline and follow-up visits.

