### Statistical analysis

Descriptive statistics will be used with measures of central tendency and dispersion for quantitative variables that have a parametric distribution; variables with free distribution will be reported in median and interquartile range and will be presented in summary measurement tables. One-way ANOVA or Kruskal Wallis test will be used to compare the effect on clinical, anthropometric, and biochemical variables between groups. An X^2^ test will be used to evaluate the effect of the intervention between groups for metabolic control goals. An intention-to-treat analysis will be performed for the three groups in the clinical trial. In addition, a per-protocol analysis will be performed on the outcome variables according to compliance with the interventions. To this end, the level of compliance with the educational modules will be measured, as well as the use of the mobile application. A repeated measures ANOVA test will also be performed to analyze the effect of the intervention in each of the groups. A logistic regression model will be used to identify the effect of the intervention on the primary target variable, A1c, as a dichotomous variable in glycemic control and uncontrol. It will be adjusted for other variables, such as intervention group, years of diagnosis, physical exercise, schooling, marital status, and occupation.

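### Body fat is measured on two different impedance devices split by clinic, but the named between-group tests have no device, clinic or baseline term: avoidable noise on secondary outcomes, not bias

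*Protocol article*

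**What the plan says.** The section on anthropometry and body composition assigns an InBody 120 to UMF 20, "while at the remaining sites (UMF 1, 4, 7, 9, and 10), an Omron body composition monitor (Omron Healthcare) will be used". It describes the technical difference itself: "The InBody 120 applies a multifrequency electrical current through hand and foot electrodes, while the Omron devices use a single-frequency current with footplate electrodes". It adds that "Both methods estimate body composition using proprietary algorithms". The same section keeps each participant on one device from baseline through follow-up.

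The Objectives section lists body fat percentage, fat mass, weight and BMI among the secondary outcomes. Skeletal muscle mass is also recorded.

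Under Statistical analysis, one-way ANOVA or Kruskal-Wallis "will be used to compare the effect on clinical, anthropometric, and biochemical variables between groups". A repeated measures ANOVA is added to look at the effect in each group. Covariates are listed only for the logistic model of A1c control, and neither clinic nor device is among them.

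The Randomization section assigns the participants of each of six clinics to the three arms. Design and setting speaks of seven clinics.

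On weight, the first paragraph of the anthropometry section says "Weight (kg) and height (cm) will be obtained for the calculation of BMI in an" InBody device with its own model code, and does not limit this to any site. Body weight and BMI then appear again in the list of variables recorded, after both impedance devices have been described.

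**The concern.** By the protocol's own description, a fat percentage read at UMF 20 and one read elsewhere come from different hardware and different undisclosed equations. There is no reason to expect them to share a zero point. A one-way test has arm as its only factor, so any offset between devices goes into the residual. The Statistical analysis section does not say whether the test is applied to 12-month values or to change, and the answer decides whether the offset matters.

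Precision on two named secondary outcomes is at stake, as is the meaning of any pooled mean fat percentage in the descriptive tables. Separately, a reader cannot tell which instrument supplies weight and BMI at the five Omron sites, or which device a seventh clinic would use.

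**Working it through.** **The plan's own figure.** Only A1c has a sample size calculation. 2 × (1.96 + 0.84)² × 1.3² / 0.5² = 105.997, so 106 per group; 106 / 0.8 = 132.5, so 133; 136 were chosen, and 3 × 136 = 408. This reproduces, and nothing below changes it.

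**Inputs for body fat.** The documents give no SD, no device offset and no site sizes. Assumed:
- offset between devices, d: 3 to 5 percentage points
- between-person SD within a device: 7 points (variance 49)
- share of patients on the InBody, p: 1/6 (six equal clinics) to 1/2
- 136 per arm, before losses; the relative results do not depend on this

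**Case 1: 12-month values compared with arm as the only factor.** The variance rises by p(1 − p)d² / 49.

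| p | d | Calculation | Rise in variance |
|---|---|---|---|
| 1/6 | 3 | 0.1389 × 9 / 49 | 2.6% |
| 1/6 | 5 | 0.1389 × 25 / 49 | 7.1% |
| 1/2 | 5 | 0.25 × 25 / 49 | 12.8% |

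The standard error of an arm difference without an offset is √(2 × 49 / 136) = 0.849 points. It becomes 0.849 × √1.026 = 0.860 at the low end and 0.849 × √1.128 = 0.901 at the high end. The loss of information equals losing about 2.5% (1 − 1/1.026) to 11% (1 − 1/1.128) of the patients.

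With wider assumptions (SD 6 to 8, d 1 to 5, p 1/7 to 1/2, 106 evaluable per arm), the variance factor runs from 1.00 to 1.17, and a nominal 80% power becomes 73% to 80%.

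**Chance imbalance in device mix.** If allocation is not balanced within clinic, the SD of the between-arm difference caused by unequal device mix is d × √(2p(1 − p) / 136): 0.14 points (p = 1/6, d = 3) to 0.30 points (p = 1/2, d = 5). This is the same noise as above: √(0.860² − 0.849²) = 0.14 and √(0.901² − 0.849²) = 0.30. It is already inside the standard error and must not be added to it.

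**Case 2: change from baseline compared.** With one device per participant, a constant offset appears in both readings and cancels, so the cost is zero.

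**Case 3: 12-month value adjusted for baseline only.** With a baseline coefficient b, an offset of d(1 − b) remains. It is removed by a device or clinic term.

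**If the devices register change differently.** Suppose the Omron records 0.8 to 1.2 times the change that the InBody records. With p = 1/6 the pooled effect, in InBody units, is multiplied by 1/6 + (5/6) × 0.8 = 0.83 up to 1/6 + (5/6) × 1.2 = 1.17. The documents give no evidence for or against such a difference.

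**Could a split by device settle that?** At p = 1/6 the InBody group has 136 / 6 ≈ 22.7 patients per arm. With SD 7 the standard error of an arm difference is 7 × √(2 / 22.7) ≈ 2.1 points, a 95% interval of about ±4. With an assumed SD of change of 3 it is about 0.9, or about ±1.75.

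**The case against.** The strongest reply is that the design already removes most of the problem. One device per participant and three arms within each clinic mean that device is not tied to arm. The Results of the study section frames the body composition aim as change, and a constant offset cancels in change. This stands, and it rules out any claim of systematic bias.

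A second reply is that site or device adjustment of a secondary outcome is normally left to an analysis plan, which is not shown. The ANOVA sentence also does not name body composition, so it is an inference that these outcomes fall under the anthropometric variables. This stands in part. The point rests on the tests that the article names, not on its silence: a one-way test cannot carry the adjustment, so an adjusted analysis would have to replace it.

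Three stronger readings are tempting and not supported:
- A reader might infer that unequal device mix creates a spurious arm difference on top of the added noise. It does not; the two are one quantity.
- A reader might infer that effects must be shown separately by device before a pooled figure is quoted. Device coincides with UMF 20 versus the other named sites, so an interaction cannot separate device from clinic, and the InBody group may be too small to be informative.
- A reader might infer that the weight statement contradicts the device assignment. The Omron assignment concerns body composition, the weight device carries a different model code, and the text neither gives that InBody to the five sites nor denies it to them. It is an ambiguity.

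**Conclusion.** The point holds as a minor one on secondary outcomes. Two technically different devices are split by clinic, and the named between-group tests have no term for device, clinic or baseline. The arm comparison is not systematically biased. Comparing 12-month values carries about 3% to 13% more variance than it needs to (standard error about 0.85 rising to 0.86 to 0.90 points). This rests on an assumed 3- to 5-point offset, an SD of 7 and an InBody share of 1/6 to 1/2, and the top of the range needs one clinic to recruit half the patients. Comparing change costs nothing under a constant offset. Pooled absolute means mix two scales in every case.

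A difference between devices in registering change is possible but only hypothetical here. The source of weight and BMI at the Omron sites and the number of clinics are unclear and need stating.

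**What to change.** - For fat percentage, fat mass and muscle mass, replace the one-way test with a linear model of the 12-month value (or change) on arm, baseline value and device or clinic. A clinic term covers device as well, because device is fixed by clinic.
- Present absolute values of these variables by device in the descriptive tables.
- Label any device-by-arm comparison exploratory, and say that it cannot separate device from clinic.
- In the anthropometry section, state which instrument supplies weight and BMI at each site.
- Reconcile the seven clinics in Design and setting with the six in Randomization and in the device assignment. If there is a seventh, name its device.

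The cost is two model terms, one table layout and two clarifying sentences. It needs no new equipment or data, since clinic, device and baseline values are known for every participant. Fixing the model before analysis also avoids a later choice between 12-month values and change.

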### Dietary measurements

A 24 h dietary recall will provide an overview of the diabetes participants' usual diet, from which the nutrition professional will evaluate the calories and macronutrients typically consumed, food quality, tastes, and preferences. The dietary measurement will be collected by the nutrition professional at each patient visit.

### Physical activity measurements

The IPAQ will be used to measure the level of physical activity. This questionnaire consists of 7 items that indicate the time of physical activities performed in the last 7 days (hours, minutes, and days per week). The physical activity will be classified after considering the METs (unit of measurement of the test) of the activity; then, physical activity will be classified in three categories: low, moderate, and high (25).

### Quality of life measurements

Quality of life will be measured using the Diabetes-39 questionnaire, which has been validated in the Mexican population. The questionnaire contains 39 items distributed in five sections: Energy-Mobility, Diabetes Control, Anxiety Concern, Social Burden, and Sexual Functioning. It is scored on a scale from 1 to 7, (1 for not at all affected and 7 for extremely affected in quality of life). The score of each section is transformed to a scale from 0 to 100 using a formula for linear conversion (26).

